#### Sample size calculation

The sample size was calculated using the G*Power software. This calculation considered the repeated measures of factorial analysis of variance (ANOVA), with an effect size (f) of 0.20, alpha value of 0.05, and beta of 0.80. The study involved three groups and two evaluation time points (pre/post), with an estimated follow-up loss of 10%. Consequently, 60 participants will be distributed as 20 participants per group: two experimental groups (B-B led by professionals and unled C-P) and one control group. The groups will be sex balanced because of the predominance of women in this type of work. In this sense, for selecting participants, we used the sex ratio of workers in group B-B (the lowest men proportion). In this site, there is a proportion of 27.1% of men and 72.9% of women; thus, our sample will try to approach this proportion in the two remaining groups.

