Finally, it is crucial to take public health measures to contribute to the reduction of sedentary behaviors in workers. Thus, we anticipate that our findings could contribute to the formulation of evidence-based interventions that can be deployed or not to improve the health and well-being of this population.

Therefore, this manuscript aims to describe the design and methods of “The Up Project,” which seeks to establish the efficacy and differences between two interventions addressed for interrupting sedentary time in desk-based workers. The principal outcomes will include variations in cardiometabolic risk factors, sedentary and physical activity levels, perception of stress, and occupational pain. Accordingly, our primary hypothesis is that both intervention groups will yield better results compared to the control group. However, we expect no discernible differences between the intervention groups due to their equivalence in duration and intensity. This is mainly because previous studies suggest that varying the frequency of breaks can improve cardiometabolic risk markers. However, studies comparing different frequencies at the same intensity and volume are lacking (34–36). In this sense, previous literature suggests that when exercise or physical activity volume and intensity are kept constant, frequency does not significantly impact muscle mass or cardiovascular risk (37, 38).

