## Discussion

### Expected results and transfer to the work context

Reducing health problems associated with sedentary behavior is a crucial concern for governments worldwide (82). While several strategies are emerging to mitigate excessive sedentary time in desk-based workers, comprehensive research examining multiple outcomes and protocols is lacking (23, 24, 33). In this context, our study will compare two intervention types (B-B and C-P) that are equivalent in duration and intensity but differ in distribution. In this sense, our primary hypothesis postulates that both intervention groups obtain better results than the control group. However, we do not anticipate significant differences between the intervention groups due to their equal duration and intensity. This design, which is more realistic for future interventions, will allow us to compare (a) the effectiveness of a continuous break protocol versus an interval-based one and (b) the effectiveness of professional-directed pauses versus autonomous breaks directed by a computational application.

Furthermore, this research helps a gap in the literature by concentrating on three pivotal facets of participants’ health. Firstly, we hope that employing DXA for body composition measurement and accelerometry for assessing sedentary and physical activity time could enhance methodological precision in this field. Secondly, we aim to explore effective strategies for enhancing cardiometabolic risk markers in desk-based workers through a more comprehensive and innovative approach. Thirdly, our objective is to contribute to developing evidence-based interventions aimed at diminishing perceived stress levels and occupational pain experienced by workers. Addressing these three indicators could be significant for companies and public health policies. In this line, our hypothesis is that both intervention groups will yield better results compared to the control group.

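### The 80% power behind N = 60 belongs to an unnamed repeated-measures ANOVA effect, not to the primary hypothesis that both interventions beat control; on change scores, power for that claim is about 57–69%

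*Protocol article*

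**What the plan says.** The Sample size calculation section gives its basis as "repeated measures of factorial analysis of variance (ANOVA), with an effect size (f) of 0.20, alpha value of 0.05, and beta of 0.80". Its last figure must be power, not beta. On the design it adds: "The study involved three groups and two evaluation time points (pre/post"), and it allows for 10% loss. The result is 60 participants, 20 per group. The section does not say whether the tested effect is time, group or group by time, gives no pre/post correlation, and gives no power for either intervention against control.

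The Background states that "our primary hypothesis is that both intervention groups will yield better results compared to the control group", and that no difference between the two interventions is expected. The Discussion (Expected results and transfer to the work context) repeats that "our primary hypothesis postulates that both intervention groups obtain better results than the control group".

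The Data analysis plan names a propensity analysis for the primary outcomes and then ANOVA or ANCOVA, chosen according to the objective. It names no contrast against control.

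**The concern.** The hypothesis consists of two comparisons, B-B against control and C-P against control, and it holds only if both are true. A three-group F test asks whether any group differs, and one effective arm is enough to make it significant. A time effect compares no groups at all. Whichever of these was entered in G*Power, the 80% attaches to a different question.

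A reader of the article will take 80% as the chance of confirming the primary hypothesis if the assumed effect is real. If the true chance is nearer 60–70%, a result in which only one arm reaches significance becomes fairly likely even when both interventions work as predicted, and it could be misread as evidence that the other arm fails.

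**Working it through.** **Inputs from the article.** f = 0.20; alpha 0.05; target power 0.80; 3 groups; m = 2 time points; 10% loss, so 60 × 0.9 = 54 analysed, 18 per group; equal effects in the two interventions (its own expectation).

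**Assumptions, because the article is silent.** f is on G*Power's group-by-time scale; contrasts are two-sided at 0.05 with the error pooled over three groups; participants are independent; the pre/post correlation ρ is 0.5, 0.577 or 0.6.

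**Step 1: reproduce 60.** λ = f²·N·m/(1−ρ), with error df N−3 and numerator df 2 for group by time or 1 for time.

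- Group by time, ρ = 0.6, N = 54: λ = 0.04 × 54 × 2/0.4 = 10.8, power 82%. N = 51 gives 79.7%, so 54 is the smallest total with equal groups, and 54/0.9 = 60.
- Time, ρ = 0.5, N = 54: λ = 0.04 × 54 × 2/0.5 = 8.64, power 82%. N = 51 gives 79.9%, so this also leads to 60.
- Group by time, ρ = 0.5: power is 73% at N = 54 and 78% at N = 60; 66 analysed would be needed.

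So 60 is reproducible, but two different effects produce it.

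**Step 2: convert f to an effect against control.** With changes (d, d, 0), the interaction cell effects have SD d·√2/6. Setting this equal to f·σ gives d = f·√18·σ = 0.20 × 4.243σ = 0.849σ.

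**Step 3: change scores.** The SD of change is σ·√(2(1−ρ)). The noncentrality of each contrast is (d/SD)·√(18/2) = 3·d/SD, on 51 df.

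- ρ = 0.5: SD = σ; noncentrality 3 × 0.849 = 2.55.
- ρ = 0.577: SD = 0.920σ; noncentrality 3 × 0.923 = 2.77.
- ρ = 0.6: SD = 0.894σ; noncentrality 3 × 0.949 = 2.85.

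**Step 4: baseline-adjusted ANCOVA, balanced baselines.** The residual SD is σ·√(1−ρ²), on 50 df.

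- ρ = 0.5: SD = 0.866σ; noncentrality 3 × 0.980 = 2.94.
- ρ = 0.577: SD = 0.817σ; noncentrality 3 × 1.039 = 3.12.
- ρ = 0.6: SD = 0.8σ; noncentrality 3 × 1.061 = 3.18.

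Power for both contrasts was simulated (1,000,000 runs), because they share the control group and the error estimate.

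| ρ | Group-by-time F | Change: each / both | ANCOVA: each / both |
|---|---|---|---|
| 0.5 | 73% | 70% / 57% | 82% / 72% |
| 0.577 | 80% | 78% / 66% | 86% / 78% |
| 0.6 | 82% | 80% / 69% | 88% / 80% |

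**Step 5: sensitivity to equal effects.** If C-P has half the B-B effect at the same f, with ρ = 0.5 and change scores, the omnibus power stays at 73% but power for both falls to 29%.

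**The case against.** The strongest reply concerns the analysis model. The Data analysis plan allows ANCOVA. If it adjusts for baseline, each contrast exceeds 80% at every correlation shown, and power for both reaches about 80% at ρ = 0.6. This stands: the size of the shortfall depends on a choice the article leaves open. It does not make the stated figure right, because the calculation is described as a repeated-measures ANOVA, and even with ANCOVA power for both is 72–78% at the two lower correlations.

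A reader might infer that 60 was certainly derived from a three-group omnibus test. The article does not support that: the effect is unnamed, and 60 also matches the time effect at ρ = 0.5. Nor does the Data analysis plan make an omnibus F test the basis of the primary conclusion, so there is no such rule to strike out. Pairwise contrasts may be left to an analysis plan that is not shown, and their absence is not the point here.

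It can also be said that the hypothesis is an expectation, not a success rule, and could be read as two separate claims. The relevant power is then that of each contrast: 70–80% on change scores, which is a smaller gap. That reading is possible, but the article says both interventions and gives power for neither.

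**Conclusion.** The point holds as a mismatch between the effect used for sizing and the primary hypothesis. It is not an arithmetic error, since 60 can be reproduced. On the calculation's own type of model (change scores), power for both contrasts is about 57–69% where the group-by-time test has 73–82%. Baseline-adjusted ANCOVA raises it to about 72–80%.

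These figures rest on 18 analysed per group, equal effects, f = 0.20 on the group-by-time scale, two-sided 0.05, independent participants and, for ANCOVA, balanced baselines. They ignore allocation by work site, the propensity adjustment and the exclusion of participants below 70% participation, all of which would be expected to lower them. They illustrate the gap and are not this trial's actual power.

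A reader might go further and conclude that power for both cannot reach 80% at this size. The documents do not support that: the correlation is not given, and on change scores with f held at 0.20 it reaches 80% at ρ of about 0.68, where the omnibus power would be about 90%.

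**What to change.** **Sample size calculation section.** Name the ANOVA effect tested and the pre/post correlation used. Say that the 80% (power, not beta) applies to that effect. Keep N = 60 and restate power for B-B against control, for C-P against control, and for both, under the planned model and with its assumptions listed, including what is ignored.

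**Data analysis plan section.** Specify the two intervention-versus-control contrasts from the baseline-adjusted ANCOVA as the test of the primary hypothesis, and conclude that both interventions are better only if both contrasts are significant. Requiring both at 0.05 needs no multiplicity adjustment for that joint claim. A contrast of the two interventions pooled against control may be added, but it is optional and does not test the joint claim.

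**Cost.** Wording in two sections and a less favourable stated power for the joint claim. No extra participants or measurements.

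### The sample-size section gives beta as 0.80 where power must be meant, and its inputs lead to 60 for the group-by-time effect only if an unstated pre/post correlation is about 0.58 to 0.60

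*Protocol article*

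**What the plan says.** The section on sample size calculation in the protocol article states: "The sample size was calculated using the G*Power software". The model is a factorial repeated-measures ANOVA, "with an effect size (f) of 0.20, alpha value of 0.05, and beta of 0.80". It continues: "The study involved three groups and two evaluation time points (pre/post), with an estimated follow-up loss of 10" per cent. The total of 60, or 20 per group, is presented as following from these inputs.

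The section does not say whether the powered effect is time, group, or group by time. It gives no correlation between the baseline and post-intervention measurements.

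The question the trial must answer is in the Background: "our primary hypothesis is that both intervention groups will yield better results compared to the control group". The Discussion repeats it under expected results.

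**The concern.** There are two separate problems.

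The first needs no assumption. Beta is the probability of missing a true effect, and power is 1 − beta. A beta of 0.80 is therefore a power of 0.20, which cannot be what was intended.

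The second is whether 60 delivers the intended 80% for the right comparison. In a design with three groups measured before and after, an intervention does better than control if its change differs from the control group's change. In the stated ANOVA that is the group-by-time interaction. The time effect only asks whether the sample as a whole changes, and could be significant if all three groups, control included, moved together. Both tests belong to the same ANOVA, but they need different numbers at the same f and the same correlation.

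If the power attached to 60 does not belong to the interaction, readers will take a null comparison with control as stronger evidence of no effect than it is.

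**Working it through.** **Inputs from the sample-size section.** f = 0.20; alpha = 0.05; power taken as 0.80; k = 3 groups; m = 2 time points; loss 10%; N = 60, so 60 × 0.9 = 54 completers, 18 per group.

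**Input not in the document.** The pre/post correlation ρ. I take 0.5 as a reference value and show 0.3 to 0.7.

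**Formulas.** Noncentral F with noncentrality λ = f²·N·m/(1 − ρ) and denominator df = (N − k)(m − 1) = N − 3. Numerator df = m − 1 = 1 for time, and (k − 1)(m − 1) = 2 for group by time. N is rounded up to a multiple of 3 for equal groups, then divided by 0.9.

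**Reproducing 60.**
- Time effect, ρ = 0.5, N = 54: λ = 0.04 × 54 × 2/0.5 = 8.64, df (1, 51), power 82.2%. N = 51 gives 79.9%, just short. So 54 is needed, and 54/0.9 = 60.
- Group by time, ρ = 0.58, N = 54: λ = 4.32/0.42 = 10.29, df (2, 51), power 80.3%. At ρ = 0.60, λ = 10.80 and power is 82.3%. On a grid of 0.01 in ρ, 54 is the number required at 0.58, 0.59 and 0.60, so this also gives 54/0.9 = 60. At 0.57 the requirement is 57; at 0.61 it is 51.

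Two readings therefore reproduce 60 exactly.

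**Group by time at ρ = 0.5.**
- N = 54: λ = 8.64, df (2, 51), power 72.6%.
- N = 60 (no loss): λ = 9.60, df (2, 57), power 77.6%.
- N = 63: power 79.8%. N = 66: λ = 10.56, df (2, 63), power 81.8%.
- So 66 evaluable are needed (64 without equal groups). 66/0.9 = 73.3, hence 74 enrolled, or 75 for equal groups.

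**Group by time over the range of ρ.**

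| ρ | Power with 54 | Power with 60 | Evaluable needed for 80% | Enrolled after 10% loss |
|---|---|---|---|---|
| 0.3 | 57.0% | 62.1% | 90 | 100 |
| 0.4 | 64.1% | 69.3% | 78 | 87 |
| 0.5 | 72.6% | 77.6% | 66 | 74 |
| 0.6 | 82.3% | 86.5% | 54 | 60 |
| 0.7 | 92.0% | 94.6% | 42 | 47 |

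**Detectable effect.** Solving the same equation for f at 80% power, ρ = 0.5 and N = 54 gives f = 0.218, about 0.22 rather than 0.20.

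**The case against.** The strongest reply is that nothing here shows the wrong effect was powered. The article does not name the effect, and the group-by-time test returns 60 just as exactly at a correlation of 0.58 to 0.60, which is plausible for pre/post data. **This stands.** A reader might infer from the match at 0.5 that the sponsor sized the trial on the time effect, or that the trial is underpowered. The document supports neither inference. The match at 0.5 depends on a value that the article does not give, and above about 0.58 the 54 completers reach 80% or more for the interaction.

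A second reply is that the shortfall is small if nobody is lost: 77.6% with all 60 at a correlation of 0.5, and above 80% from about 0.53. That is correct, but the plan itself allows for 10% loss, so 54 is the number on which its power should be judged.

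A third is that an article condenses a fuller protocol, where the menu option and the correlation may be recorded. That is fair, and the omission alone would not be a finding. But the article sets out the calculation and presents 60 as its result, and one of the figures in it is wrong as printed.

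A last reply is that any reader will see that 80% power was meant, and that the slip does not alter N. That is probably so. It is still a misstatement of a design parameter, and costs one line to correct.

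**Conclusion.** The point holds in two parts of different strength.

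- **Certain:** beta is misstated. Power of 0.80 corresponds to beta of 0.20. A reader might take the printed figure to mean that the trial was designed for 20% power; N = 60 does not bear that out, because both readings that reproduce it use power 0.80.
- **Conditional:** the listed inputs do not fix N. They give 60 for the effect that the primary hypothesis needs only if the correlation is about 0.58 to 0.60. If it is 0.5, 60 fits the time effect, and the interaction has about 73% power with 54 completers, some 7 percentage points below target. If it is 0.3 or 0.4 the shortfall is larger (57% and 64%). If it is 0.7, 60 is more than enough (92%).

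The conditional part rests on f being defined as in the formulas above, on power of 0.80 being intended, on equal groups, and on the plan's own 10% loss. It does not establish which effect the sponsor entered.

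**What to change.** Rewrite the power statement in the sample-size section so that it:
1. gives power 0.80 (beta 0.20);
2. says that the powered effect is the group-by-time interaction;
3. states the assumed pre/post correlation and its basis;
4. reports the power that 60 enrolled and 54 evaluable deliver for that effect, or the detectable f. If the correlation used was 0.5, that is about 73% at f = 0.20, or f of about 0.22 at 80% power. If it was 0.58 to 0.60, the existing 60 stands and only needs its inputs stated.

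The cost is a few lines of text and one repeat of the calculation, with no extra participants and no change to the design. The drawback is that the stated power may become less favourable.

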#### Procedures

The project will be conducted in three stages, comprising two visits to the Physical Performance and Health Laboratory of the PUCV (stage one and stage three) and one visit to the participants’ offices (stage two). Previous to measurement sessions, participants will be asked not to consume any type of stimulant prior to the measurements (such as caffeine or tea, mainly for blood pressure and heart rate). The first stage will consist of a pre-intervention measurement session in our laboratory, in which cardiometabolic risk factors, stress perception, occupational pain, physical activity, sedentary time at work, 24-h behavior, eating and smoking habits, and sociodemographic information will be evaluated. In addition, participants will be given an accelerometer, which will be removed 7 days later, and the intervention will begin once the accelerometer is removed. The intervention will have a total duration of 12 weeks, because previous literature indicates that 12 weeks is sufficient time to observe behavioral changes that can be extended beyond the time of the intervention (44). In the second stage (sixth week of intervention), the three groups will receive accelerometers to re-evaluate their daily physical activity intensity, sedentary time, and breaks in sedentary time. Finally, the third stage (post-intervention measurement) will consist of a second visit to our laboratory, where all variables will be re-evaluated. The anonymized and raw data obtained will be made available by the corresponding author upon reasonable request. A diagram of the study design, sample, and measures is presented in Figure 1.

**Figure 1 fig1:**
[figure not shown]
Study design. DABQ, Daily Activities Behavior Questionnaire.

### Main variables

In the first stage, upon arrival at the laboratory, participants will be asked to read and sign an informed consent form and then begin the measurements. First, the participant will be asked to complete questionnaires (stress perception, occupational pain, physical activity, sedentary time at work, 24-h behavior, eating habits, smoking habits, and socioeconomic status). Subsequently, the participants will be asked to enter the DXA room in the laboratory, where their height, weight, and waist circumference will be assessed. Once these measurements have been taken, the participant will be asked to lie on the scanner table for analysis. Upon completion of the scanner (estimated duration of 7 min), the participant’s resting heart rate will be determined while they remain in a lying down position. Thereafter, the individual will be requested to sit down, and their blood pressure will be measured in their left arm twice consecutively. After this, handgrip strength will be measured 2 times for each hand. Lastly, the accelerometer will be provided to the participant for a period of 7 days, for the initial measurement.

In the second stage, our research team members will go to the participants’ workplaces for the second delivery of accelerometers for 7 days. In the third stage, participants will be administered questionnaires (stress perception, occupational pain, physical activity, and sedentary time at work). Subsequently, measurements of cardiometabolic risk factors will be made with the previously mentioned protocol. All measurements will be carried out between 16:00 and 20:00 for the convenience of the participants due to their work schedule. Is important to note that all the factors chosen in this work are relevant for public health research since they are social determinants of importance for the design of public policies in our specific population.

#### Cardiometabolic risk factors

DXA scans (General Electrics, model Lunar, series 212,069, California, United States) will be used to assess body composition (fat mass, fat-free mass, and bone mass). We will use a digital balance (OMRON HN-289-LA, Kyoto, Japan) and a portable stadiometer (SECA, model 213, GmbH, Hamburg, Germany) to measure weight and height. After exhaling, waist circumference will be measured using a Lufkin metallic tape measure (W606PM, Ohio, United States) three times by the same evaluator, and the smaller measurement will be valid (45). Additionally, we will use a digital monitor (model HEM-7120, OMRON Kyoto, Japan) to measure blood pressure twice (an average will be used for the analysis), and a pulse oximeter (model Prince-100B5, Heal Force, Shanghai, China) to determine the resting heart rate. Finally, we will measure handgrip strength using a digital dynamometer (JAMAR Plus Digital Hand Dynamometer, Illinois, United States). This will be evaluated two times per hand, with the person standing and the arm extended parallel to the body. The maximum measurement per hand and an average of both measurements may be used for analysis (46). Previous studies indicate that these measurements are related to the relative risk of cardiometabolic factors (30–32, 47).

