### Sample recruitment

Desk-based workers (60 in total) will be recruited voluntarily from universities and educational institutes in the Valparaiso region, Chile. We will extend an open invitation to all desk-based workers of the Pontificia Universidad Católica de Valparaíso (PUCV) in the Faculty of Philosophy and Education and the central office located in the Central Campus. The control group sample will be obtained from Naval Academy’s desk-based workers. It is important to note that the participants of the control group are civilians or retired marines who do not undergo any type of military training or physical tests. Subsequently, our research team will be visiting their offices to conduct face-to-face recruitment. During this process, the participants will be provided a detailed description of the scientific background, research objectives, and safety measures by our research group. We aim to ensure that all participants clearly understand our research and feel comfortable participating in our study. Once accepted, they will be assigned to a group according to the work site. Upon completion of the study, the participants will be given a full report on changes in body composition, physical activity levels, and sedentary time. After the data collection period, the control group will have the opportunity to participate in the same intervention program.

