#### Booster breaks group (led breaks)

We will implement active breaks lasting approximately 14 to 16 min every working day for 12 consecutive weeks, for five workdays, excluding weekends. By implementing this approach, we can ensure that both interventions are distributed equally over time. These breaks will consist of breathing exercises, stretching exercises, and exercises recommended by the ACHS (76, 77). They will be similar in intensity to exercises proposed in the “Ponte de Pie por tu Salud” application. Each session will be divided into three parts: warm-up (2 min), main work (12 min), and cool down (1 min). The intensity of the exercises will range from light to moderate (RPE 3–4), and at the end of each session, we will evaluate intensity perception using Borg’s scale (78). Trained personnel from our research team will conduct all the sessions throughout the intervention. The intervention will be conducted in small groups (4–5 participants). While this may have a different impact on stress or motivation than the computer prompts group breaks, this is a limitation inherent to the type of intervention (22).

During the warm-up period, we will include breathing and muscle activation exercises that will last approximately 2 min. For the main work, we will target four main muscle groups: neck and shoulders, arms and wrists, lumbar back and hips, and knees and ankles, which will be distributed and combined according to Table 1.

**Table 1 tab1:** Graphical example of the time distribution of muscle groups in 1 month of intervention.

Days	Week 1	Week 2	Week 3	Week 4
Monday	i 70% - ii 30%	ii 70% - i 30%	i 70% - ii 30%	ii 70% - i 30%
Tuesday	iii 70% - iv 30%	iv 70% - iii 30%	iii 70% - iv 30%	iv 70% - iii 30%
Wednesday	i 70% - iii 30%	iii 70% - i 30%	i 70% - iii 30%	iii 70% - i 30%
Thursday	ii 30% - iv 70%	iv 30% - ii 70%	ii 30% - iv 70%	iv 30% - ii 70%
Friday	iv 30% - i 70%	i 30% - iv 70%	iv 30% - i 70%	i 30% - iv 70%

B-B, Booster Breaks group; (i) neck and shoulders, (ii) arms and wrists, (iii) lumbar back and hips, and (iv) knees and ankles. The program will be cycled over the next 2 months. Please refer to the Supplementary material for more information on the session and exercises to be implemented.

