### Data analysis plan

Owing to the characteristics of the study (i.e., cluster for conformation of the groups), allocation concealment was not possible. However, the blinding of the evaluator is detailed in the study records (more information in ClinicalTrials.gov, identifier: NCT05844267).

Descriptive data from participants will be summarized and presented as means and standard deviations for continuous variables, and frequencies and percentages for categorical variables. Appropriate statistical tests, such as T-tests or Chi-square tests, will be used to determine differences in baseline characteristics and sex differences where applicable. The normality of the variables will be explored using the Shapiro–Wilk test, and visual analysis with Q-Q plots and distribution of residuals will be applied. If the criteria associated with missing at random data are met, the relevance of the imputation will be evaluated.

For our primary outcomes, propensity analysis will be performed. This model allows us to reduce selection bias and strengthen inferences about the causal effect of an intervention in a non-randomized model (79). This analysis aims to balance the characteristics of the groups so that they are comparable in terms of all relevant variables, both known and unknown, that may influence the results. In addition, analysis of variance (ANOVA) or analysis of covariance (ANCOVA) will be applied depending on the objectives of the study. The inter-individual response of the participants will also be analyzed if deemed necessary. For our secondary objectives, we will analyze the possible mediating or moderating roles of our variables. Any additional analysis that the researchers consider necessary will be sought.

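### Waist circumference is analysed as the smallest of three tape readings; the mean of the same readings would usually be more precise and less exposed to one low reading (minor)

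*Protocol article*

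**What the plan says.** In the protocol article, under Cardiometabolic risk factors, waist circumference is taken by metal tape after exhalation, "three times by the same evaluator, and the smaller measurement will be valid". A reference is attached to the rule, but no reason for it is given. The same paragraph treats another replicated measurement differently, since the team will "measure blood pressure twice (an average will be used for the analysis").

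Under Sample recruitment, once participants accept, "they will be assigned to a group according to the work site". "The control group sample will be obtained from Naval Academy", while both intervention groups come from the university that employs the principal investigators (stated under Booster breaks group). The research team recruits at the workplaces, and it also leads the booster breaks: "Trained personnel from our research team will conduct all the sessions throughout the intervention".

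The Data analysis plan section says that allocation concealment was not possible but that "the blinding of the evaluator is detailed in the study records", and it points to the trial registry. The article does not say who takes the waist readings, beyond its being one evaluator for all three.

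**The concern.** Three readings are normally taken so that their errors can partly average out. Keeping only the lowest gives up most of that gain under ordinary reading error, and it lets a single low reading set the recorded value. A smaller waist at the post visit counts as benefit, so the rule is most sensitive to error in the favourable direction.

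The design gives this some extra weight. The control arm is a separate institution, so an evaluator who learns where a participant works also learns whether that participant is a control. Waist is one of several cardiometabolic measures, and the Background places cardiometabolic risk factors among the principal outcomes. What is at stake is some precision, and some exposure to bias, in one of these measures.

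**Working it through.** **Inputs.** From the article: three readings by one evaluator, smallest kept, at two laboratory visits. Not in the article, so assumed: independent normal reading error with SD *s*; SD of true pre–post change 2–3 cm; *s* = 0.5–1.5 cm. The article gives no figure for waist precision that could be reproduced first. Its sample size of 60 does not enter this check.

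**Step 1: error of each summary** (simulation of 2,000,000 triples, in units of *s*).
- Mean of three: variance 1/3 = 0.333, SD 0.577, no offset.
- Minimum of three: variance 0.559, SD 0.748, offset −0.846 (closed form −3/(2√π) = −0.846).
- Ratio of variances: 0.559 / 0.333 = 1.68, or about 68% more for the minimum. In reverse, the mean removes 1 − 0.333/0.559 = 40% of the minimum's error variance.

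**Step 2: does the offset matter?** The minimum sits 0.846 *s* too low at every visit. With the same *s* at both visits and in all arms, it drops out of each change score and each comparison between arms.

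**Step 3: one displaced reading.** Shift of each summary, in units of *s*:

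| One reading displaced by | Minimum | Mean |
|---|---|---|
| 2 *s* too low | −1.24 | −0.67 |
| 3 *s* too low | −2.17 | −1.00 |
| 2 *s* too high | +0.27 | +0.67 |

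In centimetres with *s* = 0.5: one reading 1 cm too low moves the minimum by 0.62 cm and the mean by 0.33 cm; one reading 1 cm too high moves them by 0.14 cm and 0.33 cm. The minimum is therefore more exposed downward and less exposed upward.

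**Step 4: effect on the change score.** Variance of change = (SD of true change)² + 2 *s*² × *v*, with *v* = 0.333 for the mean and 0.559 for the minimum.

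| SD of true change (cm) | *s* (cm) | Using mean | Using minimum | Ratio |
|---|---|---|---|---|
| 3 | 0.5 | 9.167 | 9.280 | 1.01 |
| 3 | 1.0 | 9.667 | 10.118 | 1.05 |
| 3 | 1.5 | 10.500 | 11.516 | 1.10 |
| 2 | 0.5 | 4.167 | 4.280 | 1.03 |
| 2 | 1.0 | 4.667 | 5.118 | 1.10 |
| 2 | 1.5 | 5.500 | 6.516 | 1.18 |

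Five of the six combinations lie between 1% and 10%. The corner with the smallest change SD and the largest reading error gives 18%.

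**The case against.** **The rule may be deliberate, and the ranking depends on the error model.** Readings are taken after exhaling. If errors were mainly upward (incomplete exhalation, slack tape), the smallest reading would be the better one. With exponential upward error of SD *s*, the minimum of three has variance *s*²/9 = 0.11 *s*² and the mean *s*²/3 = 0.33 *s*². This stands: the 68% holds under symmetric error and is not a general fact. The article does not claim one-sided error, and the source cited for the rule cannot be inspected here.

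**Averaging is not a cure for a failed blind.** An evaluator who pulls the tape tight on all three readings shifts mean and minimum equally. This also stands. The mean protects only against isolated low readings.

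**The evaluator may well be blinded.** A reader might infer that the people who recruit and lead sessions also measure, so that the blinding statement is contradicted. The article does not support that. It shows overlap only at the level of the research team, measurement takes place in a laboratory away from the workplaces, and the blinding details are referred to a registry record not at hand. A separate evaluator unaware of work site is compatible with every statement. The article also provides for training and standardised measurement, and it starts everyone's pre and post measurements on the same dates. Telephone follow-up is described for the computer-prompt group only; controls are reminded periodically by an unstated means.

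**Waist is one measure among many.** The Discussion presents DXA as the study's advance over BMI and waist. This stands and limits the consequence.

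**Conclusion.** The point holds as a minor one. The article fixes a rule that discards two of three readings already taken, and it averages a comparable measurement in the same paragraph. Under roughly symmetric, independent reading error, the minimum carries 1.68 times the error variance of the mean and moves nearly twice as far for one reading 2 SD too low. The 68% should not be read as the loss to the trial: change-score variance rises by about 1–10% in most of the assumed range and by 18% at its worst corner, and the constant offset cancels between arms if reading error is equal. These sizes rest on assumed SDs and on the symmetry assumption.

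Allocation by work site makes downward sensitivity somewhat more relevant, because knowing the workplace reveals control status. Whether evaluators are separate from recruiters and session leaders is an open question that the article refers to the registry. It is neither an error in the article nor evidence that the blind fails.

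**What to change.** Under Cardiometabolic risk factors, make the mean of the three waist readings the analysis value at both visits. Record and keep all three readings, and report the result based on the smallest reading as a sensitivity analysis. If the team has grounds to expect mainly upward reading error, it could instead keep the minimum and state that reason.

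The cost is one sentence and no extra measurement. The downside is that the main waist values are not directly comparable with studies that report the smallest reading; the sensitivity analysis supplies that comparison.
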